#### Shared Components

Both intervention conditions share core components that make up gold standard behavioral weight loss treatment.

##### Weight loss goals

Participants are encouraged to lose 1 to 2 lb per week and to achieve and then maintain a weight loss of 10 % of initial body weight.(Look AHEAD Research Group 2006)

##### Diet

Participants are placed on a standard calorie and fat restricted diet, with goals of 1200–1800 kcal/day and 33–42 g of fat/day (25 % calories from fat) depending on their baseline weight. This approach is typically used in behavioral weight loss programs and is consistent with AHA and ADA guidelines. (Look AHEAD Research Group 2006) Sample meal plans are provided and participants are given a fat/calorie guidebook and instructed to self-monitor their daily calorie and fat intake in their food diaries. Diaries are reviewed each week by the interventionists who provide written feedback to participants.

##### Exercise

Participants are encouraged to gradually increase their physical activity until they are exercising at least 250 min per week at moderate intensity (goal = 50-75 % of maximal heart rate, not to exceed perceived exertion of 13 on a 6–20 scale); typically by using brisk walking or another desired activity.

##### Behavior Therapy

Participants are taught standard behavioral strategies to assist in the modification of their eating and exercise habits including self-monitoring (Baker & Kirschenbaum 1993; Boutelle & Kirschenbaum 1998), stimulus control, problem-solving (Perri et al. 2001), assertiveness training, social support (Wing & Jeffery 1999), goal setting (Bandura & Simon 1977), and relapse prevention (Marlatt & Gordon 1985). For individuals who reach the weight loss goal, maintenance is emphasized. Later lessons include relapse prevention, dealing with motivation erosion, improving the quality of the diet through approaches such as volumetrics, and adding novelty to the physical activity regimen.

#### Components that differ in ABBI vs SBT

The SBT intervention addresses negative thoughts and emotions in three sessions during the first 22 weeks and reviews core skills during the reduced contact phases. To address thoughts that may impede weight loss, participants are taught to recognize a negative thought, stop it, and replace it with a positive thought. Different types of negative thoughts (rationalizations, dichotomous thinking, etc.) are described and participants practice positive ways of reframing them. To reduce stress and change eating in response to emotions, relaxation techniques are presented and distraction and increased participation in pleasurable (non-eating) activities are encouraged. This approach is sometimes described as “change-focused” because modifying negative thoughts and emotions is assumed to thereby change associated maladaptive behaviors.

In contrast, the ABBI intervention teaches acceptance, mindfulness, and values-based techniques to address negative thoughts, emotions, and food cravings (Hayes et al. 2012; Lillis et al. 2014). These techniques are taught individually (each of 3 components is taught in 2 sessions for a total of 6 sessions) and then integrated into the treatment overall. Experiential methods are utilized, where participants are presented key metaphors and engage in activities designed to illustrate key points.

Acceptance strategies are introduced by demonstrating through experiential exercises that efforts to control or avoid internal experiences have not been successful and are actually linked with unsuccessful weight control behaviors. For example, emotional eating is discussed as a way to reduce stress or sadness in the short-term, at the expense of more stress and sadness, reduced health, and possibly increased weight over the medium to long-term. Efforts to control unwanted feelings right now can often create more negative feelings and behavioral outcomes later. This is referred to as the cost of avoidance, or non-acceptance, of emotions. Alternatively, mindful acceptance is taught in relation to unwanted emotions and food cravings. A variety of exercises are used to expose participants to unwanted physiological and emotional states (through guided imagery and the presentation of desired foods), and then distress tolerance skills, such as urge surfing, are taught in vivo with unwanted emotions or cravings present.

Mindfulness techniques help participants increase awareness of their thoughts and feelings. One particular form of mindfulness emphasized in ABBI is cognitive defusion, which aims to help participants distance themselves from unhelpful thoughts without trying to change or get rid of them. The primary goal of defusion work is to de-couple problematic thoughts from unhealthy behavior. Participants are taught many strategies that include increased awareness of thoughts through meditation, thought labeling (e.g., “self-sabotaging” or “judgment”), guided imagery (e.g., imaging thoughts as leaves on a stream), thought exposure (repeating a problematic thought over and over), and metaphor (e.g., imagining your mind as a “bad motivational speaker”).

Values work helps participants identify how weight-related behaviors fit with their core values. In this context, weight influencing behaviors are seen as supporting a broader picture of desired life actions that includes possibly being active, nourishing your body, setting a good example for family members, and increasing longevity to spend more time with loved ones. Goals support values by providing tangible markers along the way, such as losing 10 lb or exercising 5 times this week, however the goals are not presumed to have any meaning or importance outside the context of stated values. The connection of weight-influencing behaviors to core values is repeatedly emphasized and presumed to sustain motivation to persist over time.

### Treatment Fidelity

Detailed patient and counselor manuals are used for all group sessions and all treatment staff are required to carefully read and review these manuals prior to session. Weekly supervision sessions are conducted with current interventionists and led by a co-investigator. In addition, all treatment sessions are audio-taped and a random set of 20 % are coded based on a standardized treatment fidelity rating form that was designed to (1) assure that core treatment elements were presented, and, (2) detect contamination of distinct intervention methods (e.g., acceptance strategies being used in the SBT condition).

### Sample Size Considerations

The primary outcome of the current study is weight loss over the 18 months in ABBI versus SBT, As we expect the variability in weight changes between individuals to be the largest at the 18-month assessment (and thus, result in larger standard deviations around mean weight losses at that time point), we conducted our power analyses to detect differences in weight loss between ABBI and SBT at Month 18. Power analyses were completed using linear mixed effects models (similar to the proposed main model) on 10,000 simulated datasets (simulations based on data from our previous pilot work). The proposed sample of 160 (n per group of 80) has 89 % power for the primary model to detect differences over time of 2.4 kg at 6 months, 3.0 kg at 12 months, and 3.6 kg at 18 months (the power for follow-up analyses detecting between-group differences each individual time point was found to be 93 % at 6 months, 85 % at 12 months, and 83 % at 18 months). The mediation analysis specified in the secondary hypothesis is exploratory in nature, and thus was not included in power analysis considerations.

### Analysis and Statistical Methods

#### Missing data

Following a documented pattern of weight regain following the cessation of treatment (Jeffery et al. 2000; Wadden et al. 2013), missing data are assumed to be missing not at random (MNAR). Thus, we use sensitivity analyses based on multiple-imputation models (Rubin 1987) to explore how robust our findings are with respect to a range of assumptions regarding missing data.

#### Primary Aim

The primary aim of the current study, examining differences in weight loss between the SBT and ABBI groups across the 18-month trial, will be investigated using a longitudinal mixed effects model. Conditionally upon finding a significant omnibus test (at α = 0.05), we will examine between-group differences at 6, 12, and 18 months.

#### Secondary Aim

The secondary aim, testing whether participants in the ABBI group experience greater improvements in acceptance of weight-related negative thoughts and distress tolerance at 6, 12, and 18 months compared to SBT participants, will be tested using a similar model to that described in the primary aim. We will further assess whether participants in the ABBI group, compared to participants in the SBT group, have better adherence to the program (assessed by session attendance) and larger changes in caloric intake/physical activity through use of generalized linear mixed models. Finally, if these between-group differences are confirmed, we will examine the extent to which changes in acceptance variables mediate differences in weight loss between the two study arms. Specifically, we will determine whether changes in acceptance from baseline to 3, 9, and 12 months mediate differences in weight loss between the ABBI and SBT groups at 6, 12, and 18 months, respectively, using a multivariate mediation model.

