#### Specific Aims

The primary aim of this study is to conduct a randomized controlled trial comparing standard behavioral weight loss treatment (SBT) with a program which combines standard behavioral weight loss components with acceptance-based strategies from ACT (which we have called Acceptance Based Behavioral Intervention or ABBI) in the treatment of overweight and obese individuals who report high internal disinhibition. We proposed a total of 160 participants who were overweight or obese and scored high on internal disinhibition.

The primary hypothesis is that participants in the ABBI program will achieve better weight losses at 6, 12, and 18 months than participants in SBT.

Secondary hypotheses are: (1) Participants in ABBI will experience greater improvements in acceptance of weight related negative thoughts and emotions and distress tolerance at 3 and 9 months than participants in SBT. (2) If the primary and secondary hypothesis #1 are confirmed, we will examine the extent to which the temporally precedent changes in acceptance of weight related negative thoughts and emotions and distress tolerance mediate subsequent differences in weight loss between the two groups.

Additional measures are included to examine the impact of the interventions on weight-related behaviors (diet and exercise) and psychosocial outcomes.

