## Method

### Study Design

The current study is a randomized controlled trial. Primary eligibility criteria are having a BMI between 25 and 50 and reporting high internal disinhibition. Potential participants are screened on the phone and must attend an orientation session and a baseline assessment appointment before being randomized to one of the two treatment groups: SBT or ABBI. Both interventions involve face-to-face group meetings weekly for 6 months, bi-weekly for 3 months, and then once per month for the final 3 months. Full assessments occur at baseline, 6, 12, and 18 months. In addition, mediators are measures at 3 and 9 months.

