### Outcome Measures

Research staff members who are blinded to participants’ treatment assignment administer all assessments. The full set of measures is collected at baseline, 6, 12 and 18 months; body weight and the proposed mediators are also assessed at 3 and 9 months so that these variables can be examined prospectively as predictors of subsequent changes in outcomes.

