##### Breath Holding

We use breath holding as an objective measures of distress tolerance because it has been shown to relate to outcomes in a variety of areas (Brown et al. 2002; Brown et al. 2009), and was shown previously to mediate the effects of an ACT-based treatment on weight control (Lillis et al. 2009). In the breath holding (Hajek et al. 1987) task, participants are asked to breathe normally for 30-s, exhale on cue, and then take a deep breath and hold it for as long as possible. Time elapsed is measured by a stopwatch. Two trials are completed and the trial of the longest duration is used. (Table 2)

**Table 2 Tab2:** Assessment schedule

Study Month	0	3	6	9	12	18
Baseline Questionnaire (Demographics)	X					
Weight	X	X	X	X	X	X
Paffenbarger	X		X		X	X
Block Food Frequency	X		X		X	X
Eating Inventory	X		X		X	X
Weight Control Strategies Scale	X		X		X	X
PROMIS Short forms	X		X		X	X
Eating Disorder Examination-Q	X		X		X	X
Bull’s Eye	X		X		X	X
Acceptance and Action Questionnaire-W	X	X	X	X	X	X
Acceptance and Action Questionnaire-II	X	X	X	X	X	X
Avoidance and Inflexibility Scale	X	X	X	X	X	X
Breath Holding	X		X		X	X

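### Secondary hypothesis 1 is stated at 3 and 9 months but analysed at 6, 12 and 18 months, and the condition for mediation shares only month 12 with the mediator windows

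*Protocol article*

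**What the plan says.** Specific Aims: secondary hypothesis 1 predicts greater improvement under ABBI in acceptance and "distress tolerance at 3 and 9 months than participants in SBT". Mediation is conditional: "If the primary and secondary hypothesis #1 are confirmed, we will examine the extent to which the temporally precedent changes" in these variables explain later weight differences.

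Study Design and Outcome Measures give the 3- and 9-month visits a purpose. The former says "In addition, mediators are measures at 3 and 9 months"; the latter that "the proposed mediators are also assessed at 3 and 9 months so that these variables can be examined prospectively" as predictors of later change.

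Secondary Aim: the same constructs are compared between arms on "distress tolerance at 6, 12, and 18 months compared to SBT participants", with a model similar to the primary one. After adding attendance, caloric intake and physical activity, the section continues: "if these between-group differences are confirmed, we will examine the extent to which changes in acceptance variables mediate" the weight difference. The mediation question is whether "changes in acceptance from baseline to 3, 9, and 12 months mediate differences in weight loss" at 6, 12 and 18 months respectively.

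Table 2 schedules the three acceptance questionnaires at all six visits (for example "Acceptance and Action Questionnaire-W X X X X X X"). Breath holding, the measure of distress tolerance, is marked only at 0, 6, 12 and 18 months.

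**The concern.** A hypothesis and the analysis of that hypothesis should refer to the same times. Here the article commits to two different sets, and nothing in it reconciles them. An analyst following the Specific Aims and one following the Secondary Aim section could reach different answers on whether secondary hypothesis 1 was confirmed, and so on whether mediation should be examined. Each could cite the protocol. That leaves a choice of time points open after the data are seen.

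The mediation argument also depends on order in time: the mediator must change before the outcome it is meant to explain. A condition for mediation resting largely on other times says little about whether the arms differed on the mediators when it matters. The distinction is practical, because contact is weekly to month 6, tapers to month 12 and then stops, so early and late differences in acceptance need not agree.

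**Working it through.** There is no figure of the plan to reproduce. The stated power concerns weight loss, and the mediation analysis was left out of it. The check compares the sets of months.

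| Set | Months | Source |
|---|---|---|
| H: hypothesis 1 | 3, 9 | Specific Aims |
| T: between-arm comparison | 6, 12, 18 | Secondary Aim |
| M: mediator windows | 3, 9, 12 | Secondary Aim |
| A: acceptance questionnaires collected | 0, 3, 6, 9, 12, 18 | Table 2 |
| B: breath holding collected | 0, 6, 12, 18 | Table 2 |

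1. **Hypothesis against test.** H ∩ T is empty: 0 of the 2 hypothesised times have a stated between-arm test.
2. **Test against mediator windows.** T ∩ M = {12}. Two of the three mediator windows (3 and 9) are not among the tested times, and two of the three tested times (6 and 18) are not mediator windows.
3. **Order in time.** The pairs are mediator change to 3, 9 and 12 months with weight loss at 6, 12 and 18 months. Month 18 is later than every mediator window and coincides with the last outcome, so a difference in acceptance there cannot precede any weight loss being explained. Month 6 coincides with the first outcome. Month 12 is a proper window, for 18-month weight loss.
4. **Acceptance data.** H and M both lie inside A. The acceptance part of the hypothesis can be tested at 3, 9 and 12 months with the data already scheduled.
5. **Distress-tolerance data.** H ∩ B is empty and M ∩ B = {12}. If Table 2 is right, the distress-tolerance part cannot be tested at the times the Specific Aims give, although Outcome Measures says the mediators are assessed at 3 and 9 months. This is a related but separate inconsistency.
6. **The condition for mediation.** The Specific Aims require both the primary hypothesis and secondary hypothesis 1. The Secondary Aim section refers only to the differences just listed, a phrase that could also take in attendance, intake and activity. The two statements of the condition therefore differ in more than their time points.

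**The case against.** The strongest reply is that this is a limited inconsistency in a condensed article. Its parts fare differently.

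- **The 3- and 9-month data would not go unused.** A reader might infer that arm differences at these visits are never tested. The documents do not support that: a mediation model ordinarily estimates the arm effect on each mediator, so months 3 and 9 would be examined once mediation is opened. What stands is that no between-arm comparison at those months is named ahead of that step. Which visits enter the similar model is not stated, and an article may leave that to the analysis plan.
- **The condition is not fully mismatched.** A reader might infer that it looks at wholly different times from the mediators. Month 12 is in both sets.
- **The condition is not shown to open on one time point.** It is tempting to say that mediation could proceed on a difference at 6 or 18 months alone, or be blocked because an early difference faded. Neither section says that one significant time point is enough. By analogy with the primary aim, confirmation could mean an omnibus test. The primary hypothesis must also be confirmed under the Specific Aims.
- **The Specific Aims are not simply right and the analysis wrong.** For breath holding, the months in the Secondary Aim section are the only post-baseline months that Table 2 supports.

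A fuller analysis plan could choose between the two sets, but it would not remove the contradiction, because the article prints both.

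**Conclusion.** The contradiction holds. As written, secondary hypothesis 1 has no stated between-arm test at either of its own time points, and the result that helps to open the mediation analysis shares one month of three with the mediator windows. The plan is wrong as written and should be fixed.

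The reach is modest. The primary weight-loss test is unaffected, and Sample Size Considerations calls the mediation analysis exploratory. Hypothesis 1 itself, however, is a named secondary hypothesis and is not labelled exploratory. No data are lost for acceptance, since the questionnaires are scheduled at every visit.

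The conclusion assumes that Table 2 shows the schedule as intended, and that the months named in the Secondary Aim section are the comparisons meant to decide the hypothesis.

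**What to change.** Use one set of time points for hypothesis 1, its test and the mediation condition, in both Specific Aims and Secondary Aim.

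- **Acceptance questionnaires.** Fit the mixed model to all scheduled follow-up visits (3, 6, 9, 12 and 18 months). Base the hypothesis 1 test and the mediation condition on the arm contrasts at the mediator windows, 3, 9 and 12 months, for example with one joint test at α = 0.05 in line with the primary omnibus approach. Report 6 and 18 months as supportive. Month 12 belongs in the test because it is the window paired with 18-month weight loss; the hypothesis in the Specific Aims would need to add it.
- **Distress tolerance.** Reconcile Specific Aims and Outcome Measures with Table 2. If Table 2 stands, test breath holding at 6, 12 and 18 months and take it out of the 3- and 9-month hypothesis.
- **Mediation condition.** State it once: that the primary hypothesis must also be confirmed, which between-group differences count, and what confirmed means.

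The cost is wording in the Specific Aims and Secondary Aim sections, with matching edits to Outcome Measures and Study Design if breath holding stays as scheduled. No new assessments are needed. The change should be made before anyone sees the mediator data by arm.

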### Assessment of Safety

The current protocol is approved by The Miriam Hospital Institutional Review Board (TMH IRB). The potential risks to participants in the current trial are considered to be minimal. The intervention recommends a weight loss of 1–2 lb per week and a diet that is balanced (with caloric intakes of 1200 to 1800 kcal/day, based on baseline weight). The physical activity recommendation is for moderate-intensity activities with only gradual increases in the amount of physical activity.

A detailed safety monitoring plan, including oversight from two external safety officers experienced with large weight management trials, has been created for the current study. Tables indicating progress with recruitment, retention at assessment sessions, reasons for dropping-out, and adverse events are submitted to safety officers annually for review. Adverse events are reported continuously to TMH IRB, and if deemed necessary the study sponsor.

### Data management, protection and confidentiality

Every effort is made to maintain confidentiality of all study participants. During the initial phone screen, potential participants are given a unique identification number (with no references to an individual’s name, address, or phone number) that is used on all documents. All data is stored in locked filing cabinets in locked rooms, or electronically on computers with secure passwords. A separate file linking study ID and participant identifiers (e.g., name, address, phone number, and contact names and addresses) is maintained in a password protected electronic file.

## Summary

The ABBI study is a randomized controlled trial comparing standard behavioral treatment (SBT) to an acceptance-based treatment (ABBI) for the purpose of improving 18-month weight loss among adults who report high internal disinhibition. The ABBI study is unique in its focus on integrating acceptance-based techniques into a SBT intervention and targeting a group of individuals with problems with emotional overeating.
